**Methods:**

A prospective longitudinal observational cohort study is conducted among patients with advanced cancer and their relatives. Patients and relatives receive a questionnaire every 3 months regarding experienced QoC and QoL during the palliative trajectory. Bereaved relatives receive a final questionnaire 3 to 6 months after the patients’ death. Data from questionnaires are linked with detailed clinical data from the Netherlands Cancer Registry (NCR). By means of descriptive statistics we will examine the experienced QoC and QoL in our study population. Differences between subgroups and changes over time will be assessed while adjusting for confounding factors.

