## Methods

### Aim

The aim of this study is to gain insight into the care experiences and QoL of patients with advanced cancer and their relatives. The following research questions will be addressed:
What is the experienced QoC according to patients with advanced cancer and their relatives?What is the experienced QoL in patients with advanced cancer and their relatives?Which factors are associated with the experienced QoC and QoL in patients with advanced cancer and their relatives?

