### Statistical analysis

We aim for a large study population of approximately 1500 patients with advanced cancer and 1000 relatives. Including a large group of patients and relatives is necessary to assess the QoC and QoL of these participants at different time points in the palliative care trajectory and its course. A study sample of this size enables us to perform subgroup analyses, for example per age group, primary tumor site, cancer treatment, diagnosis, sex, and geographical region. Also, high dropout and lower response rates due to disease-related characteristics of our study population have to be taken into account. Due to the nature of this observational study, no sample size calculations haven been performed but the number of patients are based on annual incidence of advanced cancer in the Netherlands as recorded in the NCR.

All statistical analysis will be performed using statistical packages STATA version 16. For all analyses a two-sided significance level of *p* < 0.05 will be used. Descriptive statistics (frequencies, median, mean) will be used to analyze the experienced QoC, QoL, healthcare use, advance care planning, symptom burden of patients and relatives. Further, univariate analyses will be used to analyze the crude differences between subgroups regarding QoC or QoL using parametric tests, provided that the assumptions of these tests are met. If not, non-parametric tests will be used. When testing differences between subgroups, we will adjust for confounders which are theoretically relevant and statistically associated with the outcome variable of interest. Additionally, multi-level analyses will be used to analyze the primary and secondary outcomes over time.

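### Requiring confounders to be statistically associated with the outcome before adjusting for them can leave real confounding in the subgroup comparisons, chiefly in small subgroups or when confounding opposes the subgroup effect

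*Protocol article*

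**What the plan says.** The rule stands in the Statistical analysis section of the protocol article. When subgroups are compared, "we will adjust for confounders which are theoretically relevant and statistically associated with the outcome variable of interest". The two requirements are joined by *and*. Theoretical relevance is therefore necessary but not sufficient.

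The same section sets "For all analyses a two-sided significance level of" 0.05. It gives no separate threshold for the confounder screen and does not say whether the association is tested crudely or in a model that contains the subgroup variable. The comparisons are, "for example per age group, primary tumor site, cancer treatment, diagnosis, sex, and geographical region". The target is stated as "We aim for a large study population of approximately 1500 patients with advanced cancer and 1000 relatives", and "no sample size calculations haven been performed". The section also warns that "high dropout and lower response rates due to disease-related characteristics of our study population have to be taken into account".

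The adjusted comparisons serve the third research question in the Aim section, "Which factors are associated with the experienced QoC and QoL in patients with advanced cancer and their relatives". The abstract announces them without a selection rule: "Differences between subgroups and changes over time will be assessed while adjusting for confounding factors". Nothing else in the article replaces the rule or fixes a covariate set.

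**The concern.** Confounding depends on how a factor relates to the subgroup variable and, given that variable, to the outcome. A significance test against the outcome neither defines this nor guards against missing it. The screen can go wrong in three ways:

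- **Opposing effects.** If the confounder pushes the outcome one way and the subgroup effect pushes it the other, the confounder's crude association with the outcome can shrink to nothing. It is then dropped although it matters.
- **Low power.** In a small subgroup comparison a real confounder often fails p<0.05 by chance. With several modest confounders the losses add up.
- **Ignored selection.** The reported standard error treats the chosen model as if it had been fixed in advance.

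At stake is the answer to research question 3: an adjusted subgroup difference may still carry confounding, with an interval that looks more certain than it is.

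**Working it through.** **No figure to reproduce.** The article reports no power, effect size or confounder strength. The check below asks what the rule does under assumed values. Only n=1500 comes from the document. n=300 stands for a small subgroup comparison and is an assumption, as is p<0.05 for the screen.

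**Model.** y = βx + gC + e, with x a 50:50 subgroup (SD 0.5), C a confounder with SD 1 and correlation ρ with x, and e with SD 1. Effects are in residual SD units.

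**Step 1: when a crude screen misses C.** The crude covariance of C with y is g + 0.5ρβ. With ρ=0.5, g=0.1, β=-0.4 this is 0.1 - 0.5×0.5×0.4 = 0. The confounder is real, but its crude association is nil, so it passes a 5% test only about 5% of the time.

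**Step 2: bias when C is omitted.** The bias is gρ/0.5 = 0.1×0.5/0.5 = 0.10, a quarter of the true difference of 0.4.

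**Step 3: coverage.** Without C the standard error is about 2/√n.
- n=1500: SE 0.052, and bias/SE = 0.10/0.052 = 1.92. Coverage when C is dropped is Φ(1.96-1.92) - Φ(-1.96-1.92), about 0.51. Mixing in the 5% of runs that keep C gives about 0.53.
- n=300: SE 0.115, and bias/SE = 0.87. Coverage is Φ(1.09) - Φ(-2.83), about 0.86.

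Simulation of this scenario gave 54% and 88%, in line with the formula.

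**Step 4: range over assumptions.** Simulated results, bias in SD units:

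| Screen | n | Setting | C dropped | Bias | Coverage |
|---|---|---|---|---|---|
| crude | 1500 | ρ 0.3, g 0.1, β 0 | 2.5% | 0.001 | 94.4% |
| crude | 1500 | ρ 0.3, g 0.05, β 0 | 51% | 0.009 | 95.1% |
| crude | 1500 | ρ 0.3, g 0.1, β -0.3 | 48% | 0.025 | 90.4% |
| crude | 1500 | ρ 0.5, g 0.1, β -0.4 | 95.5% | 0.096 | 54% |
| joint | 1500 | ρ 0.5, g 0.1, β -0.4 | 7.5% | 0.002 | 92.1% |
| crude | 300 | ρ 0.3, g 0.1, β 0 | 57% | 0.018 | 95.3% |
| crude | 300 | ρ 0.5, g 0.1, β -0.4 | 95% | 0.093 | 88% |
| joint | 300 | ρ 0.5, g 0.1, β 0 | 70% | 0.047 | 88.7% |
| joint | 300 | five confounders, ρ 0.3, g 0.1 each, β 0 | 63% | 0.116 | 77.5% |

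Always adjusting gave bias of at most 0.01 and coverage of 93.5-96.2% throughout.

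**Step 5: a second parameterisation.** Take residual SD 20, a true difference of -8, and a confounder correlated 0.6 with the continuous variable that is split into groups, with its effect set to cancel exactly. At n=1500 the crude screen kept it in about 5% of samples, and the mean estimate was about -6.2 to -6.3 instead of -8, a bias of about 22%. Coverage was 58-60% at n=1500 and 88-90% at n=300. With confounding in the same direction as the subgroup effect, the crude screen at n=1500 kept it every time and coverage was 95%. Across most of the n=300 settings tried here, coverage was about 83-93%.

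**Step 6: interval width.** In the cancelling case at n=1500 the mean reported SE was 0.052, against 0.060 with adjustment. In the five-confounder case at n=300 the screened estimate had an empirical SD of 0.159 but a mean reported SE of 0.126, so the interval was too narrow by about a fifth (0.126/0.159 = 0.79). The fully adjusted estimate had SD 0.143 and SE 0.143: it reports more uncertainty and yet varies less.

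**The case against.** The strongest reply is that the alarming figure is a constructed worst case. It needs both exact cancellation and a crude test, and the article commits to neither. At the full 1500, a single confounder that does not oppose the subgroup effect is either kept or too weak to matter. That stands: a reader might infer that the rule always yields biased differences, and the table shows that it does not.

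The requirement of theoretical relevance also limits spurious covariates. That is true, but it does not protect a genuine confounder from the second condition.

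Two further readings go beyond the document. A reader might extend the problem to later questionnaire waves, since dropout is expected. But the rule is attached to tests between subgroups; change over time has its own sentence on multi-level analyses, with no selection rule. A reader might also conclude that one identical covariate set is needed for every outcome. It is not: confounders can differ by outcome, and patients and relatives are separate populations.

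Finally, a covariate list and a screening threshold may sit in the full protocol or analysis plan, so their absence is no finding. What remains open to criticism is the criterion that the article does state. Research question 3 is worded as association, which softens the causal framing, but the article itself undertakes to adjust for confounding.

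**Conclusion.** The point holds in limited form. Followed as written, the rule can omit a theoretically justified confounder, pull the adjusted difference towards the unadjusted one, and understate its uncertainty. The mechanism is certain; the size is not, because it depends on confounder strength, the screening threshold and the form of test, none of which the article gives. Under the assumed values, the effect ranges from negligible (coverage near 95%) to severe (54-60% in the exactly cancelling case). At n=300 moderate undercoverage is the common result, reaching 77.5% with five modest confounders and a joint-model screen. The descriptive estimates for research questions 1 and 2 are untouched. For a mainly descriptive cohort this should be corrected, but it does not undermine the study.

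**What to change.** In the Statistical analysis section, delete the half of the condition that requires a statistical association with the outcome. State instead that each subgroup comparison is adjusted for a confounder set chosen before analysis on subject-matter grounds, regardless of p-values, and leaving out variables on the causal path from the subgroup variable to the outcome. The set may differ by exposure, outcome or population if that is justified in advance.

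Candidates are already collected. The PROFILES and NCR section lists date of birth, sex, socio-economic status, cancer type and date of diagnosis; the Questionnaires section adds educational level.

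The cost is one sentence and no new data. It is not quite free: standard errors grow by the factor 1/√(1-ρ²), about 5% at ρ=0.3 (1/√0.91 = 1.05) and 15% at ρ=0.5 (1/√0.75 = 1.15), relative to leaving the confounder out. This is felt most in small subgroups, where the chosen set should be kept short.

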### Dissemination

The funding party (Roparun) and accredited METC of this study will receive a final report of the study with recommendations. Furthermore, results of this study will be published in multiple peer-reviewed publications in scientific journals. The study aims to provide an (inter-)nationally accessible source of data. These data will be available for (internal) auditing and policy making, as all data of the PROFILES registry. PROFILES will perform first analyses on the data to check the quality and validity. After this process, the data will be freely available for research questions from other non-commercial groups in the Netherlands and abroad, subject to study question, privacy, and confidentiality restrictions, and registration [14].

## Discussion

The eQuiPe study aims to gain more insight into the experienced QoC and QoL in patients with advanced cancer and their relatives. Results from the study will raise awareness regarding the poor prognosis of advanced cancer and palliative care needs of patients and their relatives. Furthermore, the eQuiPe study is a unique national project in which many health care professionals unite to gain a deeper understanding of experienced palliative care. Results from this study will inform us on how to further improve palliative care in the Netherlands for patients with advanced cancer and their relatives.

This prospective longitudinal observational cohort study has several strengths. First, we will include about 1500 patients with solid metastasized tumor of any type and approximately 1000 relatives. Due to this large study population it is possible to assess the experienced QoC and QoL of patients and relatives at different time points in the palliative care trajectory. Moreover, this large study sample also enables us to perform subgroup analyses, for example per age group, primary tumor site, cancer treatment, diagnosis, sex, and geographical region. Second, both advanced cancer patients and their relatives are included. Our explorative qualitative study on QoL in patients with advanced cancer and their relatives, as preparation for this current study, showed that advanced cancer has a substantial impact on social engagement, social identity, and social networks for both patients and relatives [15]. Therefore, in order to improve palliative care it is of essence to focus on relatives to really comprehend their experiences. The inclusion of patients and relatives simultaneously also gives rise to the opportunity to assess them as a dyad, thus taking the interaction between patients and relatives into account. Third, the eQuiPe study is a longitudinal study. In contrast to the majority of the conducted studies on palliative care, patients and relatives will now be followed over time, from inclusion until death and thereafter for the relatives. This will provide insight in changes in their experiences over time which are currently only limitedly known to us. Fourth, our approach of including patients and relatives is highly personal. All patients and relatives will be contacted by phone by the research team to discuss participation. Participants will also be contacted by phone when they have not completed one of the questionnaires. At last, this is a national study. Already 40 of the 80 hospitals in the Netherlands are collaborating with the eQuiPe study, covering a range of academic, teaching and general hospitals and the study has a good geographic spread. Therefore, the conclusions that will follow from the results of the eQuiPe study are likely to be representative for the Netherlands and generalizable for different regions and care settings.

We also expect to encounter some challenges and potential limitations in the eQuiPe study. Firstly, selection bias cannot be ruled out because patients with a higher QoL may be more likely to participate in the study compared to patients with a lower QoL [42]. Health care professionals may contribute to this bias by only asking patients with a higher QoL to participate in our study but also patients that are self-referred may be more inclined to participate when having a higher QoL. For this reason, we emphasize during the initiation visit that professionals can ask *all patients* with metastasized disease who fulfill the inclusion criteria. Furthermore, attrition may occur because the condition of the patient might worsen over time such that further participation becomes impossible. As a result, information on the last months of life may be limited. Besides that, the life expectancy of patients varies depending on primary tumor type, which means that some patients will live for 3 months while others may live much longer. In an attempt to reduce this variation and overrepresentation of patients with advanced cancer with a relatively good prognosis, additional inclusion criteria are required for patients with breast cancer and with prostate cancer. A possible alternative for the starting point we considered was the surprise question: “Would I be surprised if this patient died in the next 12 months?”. However, according to the review of Downar at al [43]., the surprise question seems to be a poor to modestly predictive tool for patients with a near death. Therefore, we opted for an objective measure, namely having metastatic cancer. Another possible limitation is the length of the questionnaires. Due to the length, the workload for participants can become high, which can lead to a higher drop-out, especially in patients experiencing more symptoms from their disease. However, a meta-analysis showed no clear indication that response rates are attributable to the length of questionnaires [44]. A possible solution could be to use computer adaptive testing, but when using computer adaptive testing, it is of essence that all participants use the same mode (i.e., a computer) to answer the questionnaires, otherwise scores are not comparable. We wanted participants to have the option to complete questionnaires on paper as this remains a commonly preferred mode of participation [45]. At last, the clinical data are collected by the NCR, but these are mostly based on initial diagnosis and treatment. Therefore, some clinical data, for example information about treatment in the complete palliative care trajectory, will be collected via the questionnaires. However, some patients may not be fully aware of the specifics of the treatment they receive, hence, information regarding these clinical data may be incomplete.

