**Discussion:**

This study will be the first to prospectively and longitudinally explore experienced QoC and QoL in patients with advanced cancer and their relatives simultaneously. This study will provide us with population-based information in patients with advanced cancer and their relatives including changes over time. Results from the study will inform us on how to further improve palliative care.

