### Study population

All patients with a diagnosis of a solid metastasized tumor (stage IV) are eligible for inclusion. Additional inclusion criteria are required for patients diagnosed with breast cancer and with prostate cancer to reduce variation and overrepresentation of patients with advanced cancer with a relatively good prognosis. Patients diagnosed with breast cancer are eligible when their metastases are located in multiple organ systems. Patients suffering from prostate cancer are eligible when their cancer is metastasized and castrate-resistant. These criteria are based on information regarding the mean survival time of these groups (NCR). Relatives of included patients, as chosen by the patient, will also be invited to participate in the study. Patients or relatives can participate in the study irrespective of the participation of the other. Patients are also allowed to invite more than one relative to participate in the study. Table 1 provides an overview of the inclusion and exclusion criteria.

**Table 1 Tab1:** Inclusion- and exclusion criteria

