### Recruitment

Health care professionals of participating hospitals will identify patients who meet the inclusion and exclusion criteria. Health care professionals will hand out a patient information leaflet and ask eligible patients if they may be approached by the research team. The patient information leaflet will include comprehensive and understandable information regarding the study. Health care professionals will hand over the patients’ name and phone number to the research team after receiving consent from the patient, which is noted in the patient file or noted on a research sheet. These contact details will be given by phone, secured email or an online secured shared document, whichever route is preferred by the hospital. There is a possibility of self-referral for patients with advanced cancer and their relatives. Advertisement is spread via a Dutch online platform for patients and relatives who are confronted with cancer (www.kanker.nl). Patients and relatives can leave a contact request for the researcher. The recruitment procedure is similar for patients referred by their health care professional.

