#### PROFILES and NCR

PROFILES will be used for the logistics of the questionnaires. PROFILES is a registry for the study of the physical and psychosocial impact of cancer and its treatment from a dynamic, growing population-based cohort of people confronted with cancer. PROFILES follows the quality guidelines that are formulated in the ‘Data Seal of Approval’ document (www.datasealofapproval.org), developed by Data Archiving and Networked Services. The PROFILES registry is an ongoing data collection of patient reported outcomes within the sampling frame of the NCR and can be linked with clinical data of all individuals newly diagnosed with cancer in the Netherlands. For the eQuiPe study, socio-demographic and clinical data will be obtained from the NCR. Socio-demographic variables include date of birth, sex, and socio-economic status. Clinical data include cancer type, stage, and date of diagnosis.

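### Hospital coverage does not support the claim of population-based, nationally representative results, given how patients enter the study

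*Protocol article*

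**What the plan says.** The Abstract (Discussion) states: "This study will provide us with population-based information in patients with advanced cancer and their relatives". In the strengths paragraph of the main Discussion, the argument begins "Already 40 of the 80 hospitals in the Netherlands are collaborating with the eQuiPe study", adds the range of hospital types and the geographic spread, and infers that "the conclusions that will follow from the results of the eQuiPe study are likely to be representative for the Netherlands" and generalizable across regions and care settings.

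Elsewhere the article describes how patients get in:

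- Recruitment: professionals identify eligible patients and ask whether the research team may approach them. No consecutive or random sampling is described. In addition, "There is a possibility of self-referral for patients with advanced cancer and their relatives", through an online platform.
- Setting: identification takes place in medical oncology, pulmonology and/or urology.
- Study population: "Additional inclusion criteria are required for patients diagnosed with breast cancer and with prostate cancer". Table 1 requires metastases in multiple organ systems for breast cancer and castration resistance for prostate cancer.
- Discussion (limitations): "selection bias cannot be ruled out because patients with a higher QoL may be more likely to participate in the study". Professionals and self-referral are both named as possible contributors. The stated countermeasure is to stress at the initiation visit that professionals can ask every patient who meets the criteria.

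Under PROFILES and NCR, the article says that the PROFILES registry works within the NCR sampling frame and "can be linked with clinical data of all individuals newly diagnosed with cancer in the Netherlands".

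**The concern.** The inference runs from hospitals to patients. Enrolling half the hospitals, well spread, says something about regions and settings. It says nothing about which patients within a hospital are asked and agree, and that is where the article itself locates the selection.

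This matters more here than in a comparative study. Research questions 1 and 2 (Aim) ask for levels: what QoC and QoL are. Selection related to the outcome shifts a level directly, and a large sample does not reduce the shift. The confounder adjustment in the Statistical analysis section applies to differences between subgroups and does not correct an overall level. The Dissemination section foresees use for auditing and policy making, so a level read as national when it describes a healthier enrolled group could mislead users.

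**Working it through.** **1. What the hospital figures support.** 40/80 = 50% of hospitals, as the article states. The target is about 1500 patients (Statistical analysis), recruited from November 2017 to January 2020 (Setting), which is 27 months counted inclusively. That gives 1500/40 = 37.5 patients per hospital and 37.5/27 = 1.4 per hospital per month.

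The article gives no incidence of advanced cancer. As a crude scale, the Background gives almost 47,000 cancer deaths a year: 47,000 × 27/12 = 105,750 over the window. If half of these belong to participating hospitals (assumption), 1500/52,875 = 2.8%. With shares of 60% and 30% the result is 2.4% and 4.7%. All-cancer deaths are not the eligible population, and a low fraction does not itself cause bias. The figures show only that covering half the hospitals is far from covering half the patients.

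**2. Claim against entry route.**

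| Feature | Supports spread over regions and settings? | Supports representativeness of patients? |
|---|---|---|
| 40 of 80 hospitals, mixed types, good spread | Yes | No |
| Identification by professionals | Not relevant | No; selection on QoL conceded as possible |
| Online self-referral | Not relevant | No; selection on QoL conceded as possible |
| Three specialties | Not relevant | Only for patients seen there |
| Breast and prostate limits | Not relevant | Only for the restricted subsets |

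**3. How large a shift could be.** The article gives no SD, participation rate or strength of selection, so everything here is assumed: a 0-100 score with SD 20 to 25.

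Sampling error as benchmark, 1.96 × SD/√1500: 1.96 × 20/38.73 = 1.0 and 1.96 × 25/38.73 = 1.3 points.

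Model A: two equally large groups of patients whose mean scores differ by g, the better group being RR times as likely to take part. Shift = g × (RR/(RR+1) − 0.5).

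| RR | g = 10 | g = 20 |
|---|---|---|
| 1.25 | 0.6 | 1.1 |
| 1.5 | 1.0 | 2.0 |
| 2 | 1.7 | 3.3 |
| 3 | 2.5 | 5.0 |

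Model B: normally distributed score, low participation, odds of taking part multiplied by OR per SD of QoL. Shift = ln(OR) × SD.

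| OR per SD | SD 20 | SD 25 |
|---|---|---|
| 1.1 | 1.9 | 2.4 |
| 1.35 | 6.0 | 7.5 |
| 1.5 | 8.1 | 10.1 |

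The range is about 0.6 to 10 points. The weakest scenarios lie within or near sampling error; most exceed it.

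**4. What the registry could do.** The NCR items listed are date of birth, sex, socio-economic status, cancer type, stage and date of diagnosis. They contain no QoL or QoC. Take the 2.0-point shift from Model A (RR 1.5, g = 20). If these items accounted for 10% to 50% of it (assumption), calibration would leave 2.0 × 0.9 = 1.8 to 2.0 × 0.5 = 1.0 points.

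**The case against.** The strongest reply is that nothing is hidden. Selection bias is the first limitation listed, with its QoL direction and likely sources. The claim is hedged as likely, and its second half concerns regions and care settings, which the hospital mix does support. The breast and prostate limits are declared eligibility criteria with a stated reason. All of this stands: the fault is an inference that the article's own limitations undercut, not concealment. The disclosure, however, never qualifies the conclusion.

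Four stronger readings are tempting but unsupported:

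- A reader might infer that patients are hand-picked. The article says that professionals identify those who meet the criteria and can ask all of them; selective asking is a conceded risk, not the design.
- A reader might infer that reported QoC is biased upward. The limitations concede selection on QoL only, and the Background says merely that QoC and QoL may be positively associated.
- A reader might treat the missing comparison with non-participants as an error. A journal article commonly leaves that to the full protocol or analysis plan, so its absence is no finding.
- A reader might expect the registry to remove the bias. It holds neither outcome. The article describes its data as mostly from initial diagnosis and treatment, whereas Table 1 also admits patients after progression. Region, hospital type, castration resistance and metastatic sites are not among the listed items.

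**Conclusion.** The point holds as a mismatch between claim and design. Hospital coverage supports spread over regions and care settings; it does not make the enrolled patients representative or the information population-based. Descriptive QoL levels may be too favourable. For QoC the direction is uncertain.

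The size cannot be established from the article. The range of roughly 0.6 to 10 points rests wholly on the assumed selection strengths and SD, and no single value within it should be quoted as the expected bias. What is firm is that a shift of this kind does not shrink with n, while the sampling half-width at 1500 patients is already only 1.0 to 1.3 points under the assumed SD. Selection could therefore be the larger source of error without being visible in the results. The change is worth making because it affects what the study may conclude; it does not call the cohort's usefulness into question.

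**What to change.** 1. **Wording.** In the Abstract and the strengths paragraph, limit the claim to the enrolled population and to spread over regions and care settings. State that breast and prostate cancer results, including their part in tumour-site comparisons, apply only to the restricted subsets. Refer there to the selection bias described in the limitations. Cost: a few sentences.

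2. **Self-referral.** Flag self-referred participants and repeat the main descriptives without them. Cost: one recorded variable and a rerun. This tests that route only, not who is asked in hospital.

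3. **Registry comparison as a sensitivity analysis.** For participants with stage IV disease at first diagnosis, compare with NCR stage IV patients of the same period on age, sex, socio-economic status, cancer type and date of diagnosis. Add region, hospital type and survival only if available. Report calibrated QoC and QoL descriptives beside the unweighted ones. Leave breast and prostate out of the calibration if the NCR cannot apply their entry limits. Cost: an aggregated registry request, whose availability needs confirming because the linkage described covers participants, and somewhat lower precision.

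Three things stay uncorrected and should be stated as limits: selection on QoL beyond these variables, patients whose metastases came with later progression, and relatives, who are chosen by the patient and have no registry frame described (about 1000 of 2500 participants).
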